### **Outcomes**

#### *Primary outcome*

The primary outcome is the proportion of patients who are diagnosed with ARIs and prescribed antibiotics during their initial visit (defined as no prescription record at the current institution within the preceding 14 days) in both study arms. This outcome serves as the primary indicator, reflecting the overall impact of a comprehensive intervention based on CRP&SAA POCT in guiding antibiotic use for patients with ARIs. Since most self-limiting ARIs are caused by viral infections that do not require antibiotic treatment, the decline in antibiotic prescribing rates suggests that village doctors are prescribing antibiotics more judiciously. The selection of this outcome is both feasible and reliable within the context of village clinics in China. This is due to the transition of prescriptions from traditional paper documents to electronic storage, which allows for the proper preservation of prescription records, thereby ensuring data integrity and traceability.

#### *Secondary outcomes*

Secondary outcomes will be extracted from the prescribing information related to the primary outcome, as well as from subsequent visit information. In particular, we included the proportion of participants using any form of Traditional Chinese Medicines as a secondary outcome. In our previous trials, we observed an increase in the use of Traditional Chinese Medicines, possibly as an alternative to antibiotics.

These outcomes will include the following types:

1. The proportion of multiple antibiotic prescriptions in the intervention and control arms (specifically, the proportion of ARI prescriptions that include two or more antibiotics).
2. The intravenously injected antibiotic prescription rate (the proportion that contain any antibiotics delivered by intravenous injection).
3. The proportion containing any Traditional Chinese Medicines.
4. The mean cost of an ARI prescription, based on the cost of any medicines.
5. The mean cost of a consultation, based on all costs including medicines, tests and the consultation.

### *Patient safety indicator*

We will evaluate whether the intervention appears to increase the incidence of adverse events. This may occur if antibiotics are more frequently withheld for appropriate conditions as a result of the intervention. To address this concern, we will use the proportion of patients with ARIs in both the intervention and control arms who are hospitalised in Xiantao City for ARIs or sepsis within 30 days following their initial ARIs visit, excluding those who are referred by village doctors during their initial consultations, as a safety indicator.

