#### *Healthcare worker training*

After randomization, we will implement a unified and centralised training program for doctors in all village clinics within the intervention arm. The training will cover the following topics: (1) the operation process for CRP&SAA POCT; (2) recommended thresholds for CRP&SAA, along with practical case applications; and (3) clinical evaluation and management of ARIs. Following the intensive training, the research team will provide on-site guidance for the use of CRP&SAA POCT in each village clinic within the intervention arm for one week. This support will ensure that each village doctor is capable of independently operating the CRP&SAA POCT. Training will be conducted by the research team, and an online communication group will be established to address any questions that village doctors may have during the follow-up process. The research team will distribute a CRP&SAA POCT-based village clinic guidance manual on the rational use of antibiotics for ARIs to each village clinic in the intervention arm. This guideline includes an introduction to ARIs, standardised procedures for their diagnosis and treatment, CRP&SAA POCT-based clinical diagnosis and treatment pathways for ARIs, a brief overview of the principles of CRP&SAA POCT, and illustrated operational steps. Desktop reminders featuring the recommended thresholds from CRP&SAA will be distributed to the intervention arm. Village doctors in the intervention arm will be informed that the CRP&SAA recommended threshold serves only as a suggestion, and that antibiotic prescribing

must ultimately be determined based on the clinical judgment. If a village doctor believes that patients with ARIs require referral to a higher level of care, the referral should be done immediately, and CRP&SAA POCT should not be utilised. At the beginning of each month following the intervention, the research team will gather prescription information for ARIs from all village clinics within the intervention arm. The team will conduct a comprehensive assessment to determine whether village doctors are prescribing antibiotics in accordance with the CRP&SAA POCT threshold. Subsequently, the team will provide feedback to the relevant village clinics and administrative staff.

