#### **Allocation and blinding**

The 40 village clinics will be randomly assigned to one of the two arms, stratified by township, to prevent any imbalance in distribution among townships, while considering potentially significant variation in outcomes between townships. Randomisation will be conducted using R version 4.0.5 (R Foundation for Statistical Computing). ARIs patients and village doctors will not be blinded to the treatment; however, measures will be implemented to ensure a blinded outcome evaluation by employing the 'PROBE' design.

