#### *Eligibility criteria for participants*

The target population of this study included (1) patients of all ages diagnosed by a village doctor with ARIs (including upper and lower respiratory infections); and (2) patients who present with  $\geq 1$  acute respiratory symptoms (including cough, rhinitis (sneezing, nasal congestion or runny nose), sore throat, shortness of breath, wheezing or abnormal auscultation). Patients with non-respiratory diseases or those with severe clinical symptoms requiring referral to a higher-level institution are excluded from the target population.

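### The only safety indicator drops patients referred at the first visit, a decision that one-arm training could change, and no all-patient version or count of referrals is set beside it

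*Protocol*

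**What the plan says.** The section on the patient safety indicator states its purpose: "We will evaluate whether the intervention appears to increase the incidence of adverse events". The concern it names is that antibiotics may be withheld when they are needed. It then defines one measure, the proportion of ARI patients in each arm "hospitalised in Xiantao City for ARIs or sepsis within 30 days following their initial ARIs visit". The same sentence goes on to narrow the group that is counted, "excluding those who are referred by village doctors during their initial consultations, as a safety indicator". The protocol sets no other harm outcome, and no listed outcome counts first-visit referrals by arm.

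Four other places bear on who is referred:

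- **Healthcare worker training (timing and content).** "After randomization, we will implement a unified and centralised training program for doctors in all village clinics within the intervention arm". One of the three topics is "clinical evaluation and management of ARIs", and the clinics also receive a manual with diagnosis and treatment pathways. The Usual care section says that control-arm doctors get no education on ARIs.
- **Healthcare worker training (referral).** When the doctor thinks a patient needs higher-level care, "the referral should be done immediately, and CRP&SAA POCT should not be utilised".
- **Allocation and blinding.** "ARIs patients and village doctors will not be blinded to the treatment".
- **Eligibility criteria for participants.** Patients with non-respiratory disease and "those with severe clinical symptoms requiring referral to a higher-level institution are excluded from the target population".

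The Data analysis plan applies an intention-to-treat population, all ARI outpatient prescriptions, to every analysis and makes no exception for referral.

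**The concern.** Referral at the first consultation is a judgement made after the clinics have been randomised, by doctors who know their arm. Training in assessing and managing ARIs, given to one arm only, could plausibly raise or lower referral. Referred patients are likely to be among those most prone to hospital admission. If the arms refer different shares, the exclusion removes different amounts of high-risk illness from each, and what remains is no longer a comparison of randomised groups.

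This is the trial's only check that fewer antibiotics do no harm. More referral under intervention would make its remaining patients look safer than they are as a group. Less referral would do the opposite. As written, the protocol offers no means of seeing that this has happened, because referral by arm is not an outcome.

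**Working it through.** **Figures in the protocol.** None can be reproduced for this indicator: the protocol states no referral rate, hospitalisation rate or sample size for safety. The 17 clinics per arm, raised to 20 for 15% data loss (17 / 0.85 = 20), concern the primary outcome and are not in dispute. All inputs below are assumptions.

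**Calculation 1: no true difference.** Let H be the 30-day hospitalisation risk among all patients, r the share referred at the first visit, and a the share of referred patients admitted. The risk left after the exclusion is

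(H − r × a) / (1 − r).

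Take H = 2.0% in both arms, with a the same in both arms.

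| Share referred, r | a = 30% | a = 10% |
|---|---|---|
| 2% | (0.020 − 0.006) / 0.98 = 1.43% | (0.020 − 0.002) / 0.98 = 1.84% |
| 3% | (0.020 − 0.009) / 0.97 = 1.13% | (0.020 − 0.003) / 0.97 = 1.75% |
| 4% | (0.020 − 0.012) / 0.96 = 0.83% | (0.020 − 0.004) / 0.96 = 1.67% |

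Apparent risk ratios, intervention to control, when the truth is 1.00:

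- Control 2%, intervention 3%: 0.79 if a = 30%, 0.95 if a = 10%.
- Control 2%, intervention 4%: 0.58 if a = 30%, 0.91 if a = 10%.
- Equal referral: 1.00.

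The result depends heavily on a. At r = 4% and a = 30%, referred patients supply 0.012 / 0.020 = 60% of all hospitalisations; at a = 10% they supply 0.004 / 0.020 = 20%. If a equalled H, the exclusion would introduce no bias at all.

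**Calculation 2: severe and mild patients, with and without true harm.** Assume a severe share s of 1–3%, a hospitalisation risk of 20–50% if severe and 0.3% if mild, and 30% of severe patients referred in the control arm. With a fraction f of severe patients referred, the risk after exclusion is

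[s(1 − f) × h_severe + (1 − s) × h_mild] / [s(1 − f) + (1 − s)].

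One worked case, with s = 2% and severe risk 30%:

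- Control (f = 30%): (0.0042 + 0.00294) / 0.994 = 0.72%.
- Intervention, no true effect, f = 60%: (0.0024 + 0.00294) / 0.988 = 0.54%; risk ratio 0.75.
- Intervention, no true effect, f = 10%: (0.0054 + 0.00294) / 0.998 = 0.84%; risk ratio 1.16.
- Intervention, mild risk raised 1.5-fold to 0.45%, f = 60%: (0.0024 + 0.00441) / 0.988 = 0.69%; risk ratio 0.96. Counting all patients, it is 0.01041 / 0.00894 = 1.16.

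Over the whole assumed range:

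| Scenario | All patients | After exclusion |
|---|---|---|
| No effect, 60% of severe referred under intervention | 1.00 | 0.67–0.87 |
| No effect, 10% referred under intervention | 1.00 | 1.09–1.22 |
| Mild risk × 1.5, 60% referred under intervention | 1.08–1.30 | 0.78–1.21 |
| No effect, 30% referred in both arms | 1.00 | 1.00 |

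The exclusion can therefore create a benefit, create a harm, or shrink or reverse a real harm. Which of these occurs depends on a difference in referral that the protocol neither rules out nor reports.

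**Calculation 3: does counting everyone settle it?** Use a = 30% and referral of 2% against 4%, but hold the risk among non-referred patients at 1.43% in both arms. The all-patient risk is 2.00% in control and 0.04 × 0.30 + 0.96 × 0.0143 = 2.57% under intervention, a risk ratio of 1.29. That excess comes entirely from more referral admissions, with no change among patients managed at the clinic.

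**The case against.** The exclusion has a sound rationale. The indicator is aimed at harm from withheld antibiotics, and for a patient sent straight to higher care, admission may be the purpose of the referral. The exclusion also follows the eligibility section, which places patients with severe symptoms needing referral outside the target population. When referral is equal, it can even sharpen the comparison: in the worked case with mild risk raised 1.5-fold and 30% of severe patients referred in both arms, the risk ratio is 1.21 after the exclusion and 1.16 counting everyone. These are good reasons to keep the current indicator. They do not remove the selection, because the same unblinded doctors judge that eligibility after randomisation, and the safety exclusion covers anyone referred, with no severity condition.

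A reader might infer that the biomarker result itself changes who is referred. The protocol does not support that: its instruction is to refer at once and not to test, so the result can drive referral only where the instruction is not followed. What remains is the effect of training and pathways, for which the protocol gives neither direction nor size.

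A reader might also infer that the all-patient analysis should simply replace the current one. The third calculation shows why that does not follow: extra referral alone can give a risk ratio of about 1.29. The two versions answer different questions.

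Finally, the analysis plan, which is not at hand, may add sensitivity analyses. The definition of the sole safety indicator is nonetheless fixed in the protocol, and the point is confined to that.

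**Conclusion.** The point holds as a conditional one. The protocol's only harm comparison conditions on a decision taken after randomisation, by unblinded doctors trained in one arm only, and can mislead in either direction if referral differs between arms.

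Its size is unknown. Under assumed inputs, a true risk ratio of 1.00 appears as 0.58 to 0.95 when intervention clinics refer more, and as 1.09 to 1.22 in the scenarios where they refer less. It stays at 1.00 if referral is equal and there is no true effect. The reading that the indicator is biased, or that safety cannot be assessed, goes beyond the documents, because nothing in them shows that referral will differ.

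This is a worthwhile and inexpensive improvement, not a flaw that stops the trial. It matters because it changes what the trial could credibly say about safety.

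**What to change.** Keep the current indicator and pre-specify three additions:

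1. Beside it, the proportion hospitalised for ARI or sepsis within 30 days among all recorded initial ARI visits, referred or not, by randomised arm.
2. The proportion referred at the first visit, by arm.
3. A statement that a safety conclusion will be drawn only from the two versions read together, in the light of the referral proportions.

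The Data analysis plan should also say how the safety indicator's exclusion fits with its intention-to-treat population.

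The cost is one more analysis on the same hospital data. Direct admissions of referred patients add events that withheld antibiotics did not cause, which is why neither version should stand alone. The analysis also depends on referred patients having a visit record. The protocol does not say that a patient referred at once receives a prescription record, but the present exclusion already presupposes that such patients can be identified; this should be confirmed before the text is fixed. No change to any referral rule is proposed.

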### **Sample size**

Based on our exploratory study and previous research, the antibiotic prescription rate in rural primary healthcare institutions in China ranges from 50% to 80%. The minimum value of 50% is utilised as a conservative estimate of the conventional antibiotic prescription rate in the control arms. We conservatively estimate that CRP&SAA POCT intervention will lead to at least a 25% relative reduction in the antibiotic prescription rate in village clinics. Thus, to detect a reduction of 25% or more in the antibiotic prescription rate - specifically, an absolute reduction to 37.5% antibiotic prescription rate or lower - with 90% power, utilizing two-sided testing at the 5% significant level, and assuming a harmonic mean cluster size of 500 along with an intracluster correlation coefficient of 0.05, we estimate that we will require 17 village clinics per arm. Allowing for a 15% loss of prescription data and considering that 20 village clinics are required per arm, it was decided to include a total of 40 village clinics.

### **Internal pilot process**

Before initiating the main trial, we will evaluate the feasibility of implementing the intervention through an internal pilot process. During the preparation period, 8 village clinics (from 4 townships) will be selected as pilot sites and randomly assigned to either the intervention or control arm. They will be followed up for one month to evaluate the feasibility of the following objectives: (1) whether all village doctors in the intervention arm can independently operate the CRP&SAA POCT; and (2) whether the doctors can effectively guide the antibiotic prescription for patients with ARIs based on the varying cut-off thresholds of the CRP&SAA POCT. We will adjust the implementation plan as necessary based on the insights gained from the internal pilot process.

### **Data analysis plan**

All analyses will be conducted on the intention-to-treat (ITT) population, defined as all outpatient prescriptions issued by village clinics for ARI patients, regardless of the compliance of village doctors and patients with the intervention. For the primary and secondary outcomes, which are binary variables, we will employ Generalised estimating equations (GEEs) to estimate both relative and absolute measures of effect. The same methods will be used to analyse the mean cost of an ARI prescription and a consultation. The primary outcome will also be analysed in subgroups based on ARI

patient's age (1-15 / 16-65 / over 65 years old), ARI patient's sex (male / female), type of ARI (upper respiratory tract infection / lower respiratory tract infection), and season. Likelihood ratio tests will be employed to assess the heterogeneity of antibiotic prescribing across these different subgroups. We also will conduct per-protocol analyses, which included only ARI patients who received CRP&SAA POCT in village clinics within the intervention arm. Furthermore, modified poisson regression and linear regression models, which account for village-level clustering using the clustered sandwich estimator, will be employed to replicate all results and assess their robustness. No interim analyses are planned, and all outcomes will be analysed following data collection.

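### The ITT set is built from prescriptions issued, but the primary outcome counts patients at initial ARI visits; the effect may be biased if some visits leave no prescription record

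*Protocol*

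**What the plan says.** The Data analysis plan applies one population to all analyses: the "intention-to-treat (ITT) population, defined as all outpatient prescriptions issued by village clinics for ARI patients". The unit is a prescription, and having been issued one is the condition for entry.

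The Primary outcome section uses a different unit. It is "the proportion of patients who are diagnosed with ARIs and prescribed antibiotics during their initial visit", where an initial visit is "defined as no prescription record at the current institution within the preceding 14 days". The participant eligibility criteria refer to a village doctor's ARI diagnosis and to presenting respiratory symptoms; neither requires that anything be prescribed.

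The Secondary outcomes mix the two units. Multiple prescribing is "the proportion of ARI prescriptions that include two or more antibiotics", a prescription denominator, while the last cost outcome is "The mean cost of a consultation, based on all costs including medicines, tests and the consultation", which is a consultation measure. The Patient safety indicator counts ARI patients hospitalised within 30 days of their initial visit.

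The stated reason for choosing the primary outcome is "the transition of prescriptions from traditional paper documents to electronic storage, which allows for the proper preservation of prescription records". The protocol does not say whether a visit at which no medicine is given creates a record in that system.

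**The concern.** Three things follow if the Data analysis plan is applied as written.

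- **Entry depends on a consequence of treatment.** Training, testing, feedback and leaflets all aim to change what the doctor prescribes. An ARI patient sent home with nothing is a case in which the intervention may have worked fully, yet that patient is not in the set. Selecting on a post-randomisation behaviour removes the protection of randomisation, whatever the set is called.
- **The unit is wrong for the primary outcome.** Prescriptions from repeat visits fall inside the stated population, although the outcome is confined to initial visits.
- **The look-back has the same weakness.** It searches for any prescription record, not an ARI visit. A patient with a recent unrelated prescription has a new ARI excluded. A patient whose first ARI visit produced no prescription has the return visit counted as initial.

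Safety is also affected. The indicator exists because antibiotics might be withheld when they are needed. Patients who left with no prescription belong to that group, and the rule for all analyses would drop them.

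**Working it through.** **1. The plan's own figure.** Inputs from the Sample size section: 50% v 37.5%, 90% power, two-sided 5%, 500 per clinic, ICC 0.05, 15% loss.

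- Design effect: 1 + (500 − 1) × 0.05 = 25.95.
- Patients per arm without clustering: 329 (pooled variance) or 325.7 (unpooled).
- Clinics per arm: 329 × 25.95 / 500 = 17.08, or 325.7 × 25.95 / 500 = 16.9.
- After the loss allowance: 17 / 0.85 = 20.

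The stated 17 and 20 reproduce, and this point leaves that arithmetic untouched. With 20 clinics of 500 the effective number per arm is 20 × 500 / 25.95 = 385, and power is about 94%.

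**2. What a prescription-only denominator does.** Let p be the antibiotic rate over all initial ARI visits and q the share of those visits with no prescription. All antibiotic visits stay in the set, so:

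- observed rate = p / (1 − q)
- observed RR = true RR × (1 − q_control) / (1 − q_intervention)
- with equal q, observed RD = true RD / (1 − q)

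**3. Results over assumed shares.** The protocol gives no value of q. The rows below are assumptions and take 50% and 37.5% as per-visit rates. Power is the normal approximation for two proportions at 385 per arm, with cluster size held at 500.

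| q control / intervention | Observed rates | Difference (points) | RR | Power |
|---|---|---|---|---|
| 0 / 0 | 50.0% v 37.5% | 12.5 | 0.75 | 94% |
| 5% / 5% | 52.6% v 39.5% | 13.2 | 0.75 | 96% |
| 10% / 10% | 55.6% v 41.7% | 13.9 | 0.75 | 97% |
| 2% / 5% | 51.0% v 39.5% | 11.5 | 0.77 | 90% |
| 0 / 5% | 50.0% v 39.5% | 10.5 | 0.79 | 84% |
| 5% / 10% | 52.6% v 41.7% | 11.0 | 0.79 | 86% |
| 0 / 12.5% | 50.0% v 42.9% | 7.1 | 0.86 | 51% |
| 5% / 2% | 52.6% v 38.3% | 14.4 | 0.73 | 98% |

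Example: 0.375 / 0.95 = 0.395, so the difference is 0.500 − 0.395 = 0.105 and the RR is 0.75 / 0.95 = 0.79. The 0/12.5% row is the case in which every avoided antibiotic (50 − 37.5 = 12.5 points) leaves no prescription at all: 0.375 / 0.875 = 0.429.

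**4. Reading the table.** With no lost visits there is no bias. Equal loss leaves the RR alone and inflates the difference. More loss under the intervention pulls the RR towards 1; less loss pushes it away from 1.

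**The case against.** The strongest reply is that the prescription record may be this system's encounter record. The cluster eligibility criteria verify average weekly ARI visits from prescription data. The Secondary outcomes are drawn from the prescribing information, together with later visit information, and include the cost of tests and of the consultation. If every visit creates such a record, nothing is lost. The Secondary outcomes section also reports that Traditional Chinese Medicine use rose in the team's earlier trials, possibly in place of antibiotics; those visits would stay in the denominator. Both arguments stand as reasons why q may be small. Neither shows that it is zero.

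It can also be said that the two definitions are nested: a broad set of prescriptions, then a restriction to initial visits. That would deal with repeat prescriptions. It would not restore visits with no prescription, and it would leave the look-back as it is.

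The planning rates may already be on a prescription denominator, since the Sample size section calls them antibiotic prescription rates. In that case, dividing them by (1 − q) would not apply. The table therefore illustrates how the mechanism works and does not forecast this trial.

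A reader might infer more than the documents support:

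- **That the effect is biased as a matter of fact.** This needs a share above zero for the difference, and a share that differs by arm for the RR. Neither is documented.
- **That a spurious benefit will appear because the paid test creates a record in one arm only.** With no true effect, losing 5% to 15% of control visits and no intervention visits would give 0.50 / (1 − q) − 0.50 = 2.6 to 8.8 points. But nothing says that payment for the test creates a prescription record, and testing is optional and needs consent, so complete capture in that arm is unlikely.

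**Conclusion.** The contradiction in unit and denominator is in the text, and nothing in the protocol resolves it. Followed literally, the population rule admits repeat prescriptions, and it drops ARI patients without a prescription from both the primary and the safety denominators. That is enough to require a correction before data are extracted, because a file of prescriptions alone can neither reveal nor repair the selection later.

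The size and sign of any bias are not established. Dilution is the likelier direction if antibiotics are withheld without a substitute. In that case, assumed shares of 0/5% to 0/12.5% turn a 12.5-point difference into one of 10.5 to 7.1 points, and an RR of 0.75 into 0.79 to 0.86. If no visit is lost, the effect of this selection is nil. The look-back fault follows from the wording alone, but no difference between arms has been shown for it.

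**What to change.** 1. Define the primary and safety analysis population as all initial ARI visits at randomised clinics, one per patient-episode, whether or not a medicine is prescribed. Draw them from the encounter or consultation records that the consultation-cost outcome needs.
2. Define an initial visit as one with no ARI visit at that clinic in the preceding 14 days, in place of no prescription record of any kind.
3. State whether a visit without medicines creates a record, and report the share of ARI visits without a prescription by arm.
4. Keep the prescription-only denominator as a sensitivity analysis.

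The cost is revised wording and one altered data extract; no further clinics or patients are needed. It does depend on visits without medicines being recorded. If they are not, the protocol should describe the effect as conditional on a prescription having been issued, and name that selection as a limitation. If every visit does create a record, a sentence saying so settles the no-prescription question, and only the unit and the look-back remain to be corrected.

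### The intention-to-treat set is defined by prescriptions issued, not by patients with ARIs, so visits ending without a prescription may be left out; this can bias the primary and safety comparisons if their share differs by arm

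*Protocol*

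**What the plan says.** The Data analysis plan states: "All analyses will be conducted on the intention-to-treat (ITT) population". It defines that population by documents issued rather than by people seen: "defined as all outpatient prescriptions issued by village clinics for ARI patients".

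Other sections count patients:
- Eligibility criteria for participants: the target population is patients whom a village doctor diagnoses with an ARI. Receiving a prescription is not a condition.
- Primary outcome: "the proportion of patients who are diagnosed with ARIs and prescribed antibiotics during their initial visit".
- Patient safety indicator: the denominator is patients with ARIs in each arm. The stated worry is that harm could follow from withholding: "This may occur if antibiotics are more frequently withheld for appropriate conditions as a result of the intervention".

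The Primary outcome section also ties the initial visit to prescriptions ("defined as no prescription record at the current institution within the preceding 14 days") and justifies the outcome by the move to electronic storage, "which allows for the proper preservation of prescription records". No section says how a visit that ends without a prescription is captured.

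**The concern.** A trial of whether doctors prescribe should not define its analysis set by whether something was prescribed. Under the literal definition, an ARI patient who is assessed and sent home with advice only is not analysed. That decision is made after allocation by doctors who know their arm. In the intervention arm it is made under training, feedback and patient leaflets that discourage unnecessary antibiotics. The intervention targets antibiotics, but it may also change, indirectly, how often a patient leaves with nothing.

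Three things are at stake:
- **Primary comparison.** Dropping antibiotic-free visits raises the observed antibiotic rate. If more are dropped in one arm, the effect estimate shifts.
- **Initial-visit rule.** A patient who left without a prescription and returns within 14 days for an antibiotic has no prior prescription record. The return is then scored as an initial visit with an antibiotic, and the true first visit is absent.
- **Safety.** Patients sent home with nothing are part of the group that the safety indicator is meant to watch, yet they would be outside its denominator.

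**Working it through.** **Inputs from the protocol (Sample size):** control rate 50%, intervention rate 37.5%, two-sided 5% test, 90% power, cluster size 500, ICC 0.05, 15% data loss, 20 clinics per arm.

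**Input not in the protocol (assumed):** *s*, the share of non-antibiotic patients who leave with no prescription of any kind, by arm.

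**1. The plan's own figure.** Design effect = 1 + 499 × 0.05 = 25.95. Individuals per arm with unpooled variance = (1.960 + 1.282)² × (0.25 + 0.234375) / 0.125² = 325.7. Clinics = 325.7 × 25.95 / 500 = 16.9, so 17. With the allowance, 17 / 0.85 = 20. The stated 17 and 20 reproduce.

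**2. Observed rate under the prescription denominator.** Dropped patients have no antibiotic, so the numerator is unchanged and the denominator shrinks: observed = p / (1 − (1 − p)s).

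For example, with s = 10% in the intervention arm: 0.375 / (1 − 0.625 × 0.10) = 0.375 / 0.9375 = 40.0%.

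| s control / s intervention | Control | Intervention | Difference (points) | Ratio | Power, 20 clinics per arm |
|---|---|---|---|---|---|
| 0% / 0% | 50.0% | 37.5% | 12.5 | 0.75 | 93% |
| 0% / 2% | 50.0% | 38.0% | 12.0 | 0.76 | 91% |
| 0% / 5% | 50.0% | 38.7% | 11.3 | 0.77 | 87% |
| 0% / 10% | 50.0% | 40.0% | 10.0 | 0.80 | 78% |
| 5% / 20% | 51.3% | 42.9% | 8.4 | 0.84 | 63% |
| 10% / 10% | 52.6% | 40.0% | 12.6 | 0.76 | 93% |
| 20% / 20% | 55.6% | 42.9% | 12.7 | 0.77 | 93% |

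Power uses 20 clinics of 500 per arm, ICC 0.05 and a noncentral t with 38 degrees of freedom; cluster size is held at 500. The last two rows show that equal shares change the result little.

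**3. Initial-visit rule.** Take 5% / 20% and assume that 20% of the dropped patients return within 14 days and get an antibiotic. Per 100 true initial visits:
- Intervention: 12.5 dropped, 2.5 return, (37.5 + 2.5) / (87.5 + 2.5) = 44.4%.
- Control: 2.5 dropped, 0.5 return, (50 + 0.5) / (97.5 + 0.5) = 51.5%.

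The difference falls from 8.4 to 7.1 points.

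**4. Opposite direction.** Suppose a test order alone creates a record. Drug-free tested visits are then kept in the intervention arm, while control clinics have no kits. With no true effect (50% v 50%) and drug-free visits lost in control only, s = 10% gives 0.5 / 0.95 = 52.6% and s = 20% gives 0.5 / 0.9 = 55.6%. These are false benefits of 2.6 and 5.6 points.

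**5. Safety.** Assume that 1% of all ARI patients in an arm are hospitalised and 10% of all visits are missing. Observed rate = (1% − 0.10 × r) / 0.90, where r is the risk among the missing:
- r = 0.2%: 1.09%
- r = 1%: 1.00%
- r = 2%: 0.89%

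The observed rate can be too high, right or too low.

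**The case against.** The strongest reply is that the loss is not documented. No section says that any ARI visit ends without a record, and the protocol may use prescription data loosely to mean the visit record. The cluster eligibility criteria verify weekly ARI visits from prescription data. The monthly feedback checks adherence to the threshold from prescription information, which requires seeing patients who were not given an antibiotic. One secondary outcome is "The mean cost of a consultation, based on all costs including medicines, tests and the consultation", so the data appear to hold more than medicines. This makes a benign reading plausible, but it does not show that a drug-free visit creates a record, and the Data analysis plan says otherwise on its face.

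The second reply is that the intervention aims at antibiotics, not at whether anything is prescribed. The Secondary outcomes section reports more use of Traditional Chinese Medicines in the team's previous trials, possibly in place of antibiotics. Such substitution keeps patients in the data and may make the shares small. This stands as a limit on size. It does not remove the problem, since the protocol does not show that substitution is complete.

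Third, a higher no-prescription share in the intervention arm makes the efficacy result conservative. That is true, but it costs power, and the direction is not assured: step 4 of the working runs the other way.

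A reader might infer that both the primary and safety results are certainly biased, or that the intervention is designed to change who receives any prescription. The documents support neither. Bias needs unequal shares, no shares are given, and an effect on having any prescription would be indirect.

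**Conclusion.** The inconsistency is real and lies in a stated definition, not in a detail that could be left to an analysis plan. The Data analysis plan counts prescriptions, while the eligibility criteria, primary outcome and safety indicator count patients. Taken literally, the analysis set depends on a post-randomisation decision by unblinded doctors and is not intention-to-treat.

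The harm is conditional. If the no-prescription share is higher in the intervention arm, the planned 12.5-point difference shrinks to between 11.3 and 8.4 points in the illustrated range of 0% v 5% to 5% v 20%. If shares are equal, little changes. If drug-free visits are recorded only where a test was ordered, a benefit can appear where none exists. All these shares are assumptions. For safety, neither direction nor size can be fixed without knowing the risk of the missing patients, so the text does not support a claim that harm will be understated.

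**What to change.** Redefine the intention-to-treat population in the Data analysis plan as all eligible initial ARI consultations at randomised clinics, whether or not a prescription was issued, identified by the same rule in both arms. Then:

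- Score a consultation with no prescription as no antibiotic.
- Define the initial visit by no prior ARI consultation at the clinic within 14 days.
- Use the same denominator for the safety indicator, keeping its stated exclusion of referred patients.
- Make the consultation the condition for entry, so that no visit enters the data in one arm only because a test was ordered.
- Report the no-prescription share by arm.

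The protocol does not name a visit log or billing record, so a fallback is needed. If drug-free visits are not recorded in the clinic system, say so, report ARI record counts per clinic by arm, and add a sensitivity analysis over a range of no-prescription shares that may differ by arm.

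The cost is protocol wording and a wider data extraction. Where drug-free visits are recorded incompletely, the prescription-based result should be shown alongside. The planned 17 and 20 clinics per arm need not change.
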